## Methods

### Study Design

We will utilize a stepped wedge cluster randomized trial to implement BSMART. BSMART will be sequentially rolled out to 15 participating HIV treatment and care facilities assigned in three steps (Table 1). Each step will provide data for a 12-month control/pre-implementation, a 12-month implementation, and a 12-month maintenance period. We will stratify Botswana's HIV treatment and care facilities into three levels of facilities. We will randomly assign each of the three levels of facilities to one of three study steps. Each step will comprise (i.e. have representation) from three levels of facilities, giving each level of facilities the same probability of beginning the intervention at any step). We choose this design to:

- 1) minimize the practical, logistical, and financial constraints associated with large-scale project implementation,
- 2) control for the effect of time, and
- 3) ensure that all HIV treatment and care practices will eventually offer the intervention and assess maintenance.

The study will screen approximately 6,900 HIV-infected patients and we expect to enroll 750 eligible participants, 375 of whom will participate in the pre-implementation phase and 375 of whom will participate in the implementation phase across three waves of implementation at five facilities each.

| Table 1: Time Periods for Stepped Wedge Implementation |                                                  |         |                |                |                |             |
|--------------------------------------------------------|--------------------------------------------------|---------|----------------|----------------|----------------|-------------|
| Steps                                                  | Total Number of Participants                     | Year 1  | Year 2         | Year 3         | Year 4         | Year 5      |
| 1                                                      | 5 facilities, n=250 PLWH (1DH, 2 PHs, 2 clinics) | Control | Implementation | Maintenance    |                |             |
| 2                                                      | 5 facilities, n=250 PLWH (1DH, 2 PHs, 2 clinics) |         | Control        | Implementation | Maintenance    |             |
| 3                                                      | 5 facilities, n=250 PLWH (1DH, 2 PHs, 2 clinics) |         |                | Control        | Implementation | Maintenance |

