## Power and Sample size

Our sample size is based on the hypothesis that interventions will have a substantial impact on primary endpoints compared to the control phase (Figure 5).

**Main effect:** Based on a meta-analysis of 24 randomized controlled trials in LMIC, smoking abstinence at 6 months follow-up ( $P_{\text{control}}$ ) for usual care averages 10% (range, 8% to 14%). Assuming withdrawal from trial follow-up or loss to follow-up to be 5%, our sample of 25 PLWH per cluster per period has power of 87% to detect at least 10% increase (main effect,  $\Delta = (P_{\text{implementation}} - P_{\text{control}})$ ) in the primary endpoint at six months with the assumption that the event rate for those in control phase is 10% and two-sided alpha at intra-cluster correlation of 0.02.

[figure not shown]

Fig 5. Power to detect primary endpoint, main effect versus standard of care (SOC)

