## Statistical analysis

### Statistical Analysis for Study Objective 1.

We will analyze “Reach” as the percentage of PLWH who participated in the screening for tobacco use for each facility and compare between the control and implementation group using chi-square test. We will examine sociodemographic and clinical characteristics of smokers who did not participate. As analysis of primary outcome with intention-to-treat, the clinical effectiveness endpoint will be compared between the control group and implementation group at the individual level with a generalized linear mixed model with a binary distribution using the jack-knife method to estimate standard errors to account for grouping within clusters and by incorporating a log-link function to estimate the relative risk as a measure of effect. We will include random effects to account for the clustering within facilities and periods and fixed effects for type of facilities. The model will be selected as the best model with unique covariance structure that produces the lowest Bayesian Information Criterion (BIC) value. The covariance structures that will be considered in the model are the first order of autocorrelation covariance structure, unstructured covariance structure, and Toeplitz covariance structure. We will use the Satterthwaite method to adjust for denominator degree of freedom for the test for fixed effects. The random coefficients will be modeled using G-side random effects, and we will obtain the subject-specific estimates by defining the appropriate variance-covariance structures.

Sex-stratified and age-stratified analyses and models will be performed as secondary analyses. Given high quality of data and experience in conducting studies in Botswana, we do not expect to have missing observations in the variables required for the primary analysis. To address the concern about contamination, we will conduct a sensitivity analysis excluding patients in the control group in the 90 days before crossing over to the implementation group. Because there will be fewer than 50 clusters, we will conduct a sensitivity analysis using a small sample correction with the Kenward-Roger method.

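### The primary test pairs a 15-facility jackknife standard error with Satterthwaite degrees of freedom that may not match it; under the model as written, type I error can reach about 5.5–7%.

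*Protocol*

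**What the plan says.** All the elements are in the protocol, under Statistical Analysis for Study Objective 1. The primary endpoint is analysed with a log-link mixed model for a binary outcome, "using the jack-knife method to estimate standard errors to account for grouping within clusters". Random effects cover facilities and periods, and facility type is a fixed effect. No fixed calendar-period term is listed. The covariance structure is chosen by BIC. For the test itself: "We will use the Satterthwaite method to adjust for denominator degree of freedom for the test for fixed effects". A further small-sample method is placed outside the primary analysis: "Because there will be fewer than 50 clusters, we will conduct a sensitivity analysis using a small sample correction with the Kenward-Roger method".

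The number of clusters comes from Study Design: "BSMART will be sequentially rolled out to 15 participating HIV treatment and care facilities assigned in three steps". Each facility contributes one control year and one implementation year to the primary comparison. The protocol does not say whether the Satterthwaite df are to be computed for the jackknife variance or for the model-based variance, and it gives no numeric alpha.

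**The concern.** A standard error and the degrees of freedom used with it should describe the same variance estimate. Satterthwaite df, as usually computed, measure how precisely the model-based variance is known. The jackknife variance comes from 15 leave-one-facility-out estimates, so it is known only about as well as 15 facilities allow, however stable the model-based variance looks.

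The mismatch bites at the planned size. With about 24 analysed participants per facility and period and an intra-cluster correlation of 0.02, the facility-by-period variance is often estimated at its boundary of zero. The model then attributes almost no uncertainty to between-cluster variation and the df become effectively infinite. The p-value and confidence interval of the primary analysis are then read against the normal distribution although the standard error rests on 15 units. At stake is the calibration of the main effectiveness test and the width of its interval. A borderline result could be declared significant for this reason alone.

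**Working it through.** **Inputs from the protocol.** 15 facilities; 25 participants per facility-period; control rate 10%; 5% loss, so 25 × 0.95 = 23.75 analysed (24 in the simulations); ICC 0.02. **Assumed, because not given:** alpha 0.05 two-sided (the text reads only "two-sided alpha at intra-cluster correlation of 0.02") and cluster autocorrelation between a facility's two years, run from 0.5 to 1.0.

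**Step 1: the protocol's own figure.** The power section states "our sample of 25 PLWH per cluster per period has power of 87% to detect at least 10% increase". The design effect is 1 + (23.75 − 1) × 0.02 = 1.455, so the effective n per condition is 15 × 23.75 / 1.455 = 244.8. For 10% against 20% at alpha 0.05, a two-proportion calculation gives 87.5% (87.9% with unpooled variance). The 87% is reproduced, so these inputs are a fair basis for what follows. That calculation uses normal critical values.

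**Step 2: size of the mismatch in theory.** If a statistic truly follows t with 14 df, its rejection rate depends on the reference used:

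| Reference df | Critical value | Rejection rate |
|---|---|---|
| 14 | 2.145 | 5.0% |
| 28 | 2.048 | 6.0% |
| 50 | 2.009 | 6.4% |
| 700 or normal | 1.96 | 7.0% |

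The ceiling is therefore about 7%. The interval is at most 1 − 1.96/2.145 = 9% too narrow.

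**Step 3: simple jackknife check.** 100,000 null trials per setting were run with 10% abstinence in both phases. Facility effects were on the log scale with variance ln(1 + 0.02 × 0.9/0.1) = ln 1.18 = 0.166. The estimate was the log risk ratio of pooled proportions with a delete-one-facility jackknife. Against 1.96 the rejection rate was 6.5–6.7%; against t with 14 df it was 4.5–4.7%. A repeat with 60,000 trials per setting gave 6.4–6.6% and 4.5–4.7%.

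**Step 4: the model as written.** A log-link mixed model was fitted with phase and facility type fixed, and the jackknife refitted 15 times per trial. Satterthwaite df came from the model-based variance. There were 3,000 trials per setting (Monte Carlo standard error about 0.4 points).

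| Random effects | Autocorrelation | Facility-period variance estimated as 0 | Jackknife + Satterthwaite | Jackknife + t14 |
|---|---|---|---|---|
| Facility and facility-period | 1.0 | 57% | 6.7% | 4.5% |
| Facility and facility-period | 0.8 | 48% | 6.2% | 4.7% |
| Facility and facility-period | 0.5 | 38% | 5.5% | 4.1% |
| Facility only | 1.0 | not fitted | 7.0% | 4.7% |
| Facility only | 0.8 | not fitted | 7.0% | 4.8% |
| Facility only | 0.5 | not fitted | 6.5% | 4.3% |

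With facility and facility-period effects, the mean jackknife standard error matched the true spread of the estimate (for example 0.227 against 0.227 at autocorrelation 1.0). The standard error is not biased, so the excess comes from the reference distribution.

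A separately coded simulation (3,000 and 4,000 trials per setting, autocorrelation 0.6 and 0.9) gave 5.8–6.8% as written and 4.5–4.8% with 14 df. The facility-period variance was zero in 41–54% of its trials.

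**Step 5: with fixed calendar-year terms added.** The as-written test fell to 4.0–4.5% in the first simulation and 3.7–4.2% in the second. In the first, the jackknife standard error was then too large (mean about 0.35–0.36 against a true spread of 0.31–0.33), and the 14-df reference gave 2.6–3.5%.

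**The case against.** Several points on the other side have force.

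- **The primary test is not left without a small-sample adjustment.** A reader might infer this because the fewer-than-50-clusters reasoning appears only beside Kenward-Roger. The documents do not support it: Satterthwaite df are themselves such an adjustment. The fault is that they may not fit the variance they are used with.
- **The direction depends on modelling choices.** Study Design says the stepped wedge was chosen in part to control for time. If calendar-year terms enter the model, the inflation disappears. That stands, but the analysis section lists no such terms, so it does not rescue the test as written.
- **Only some readings were simulated.** BIC selection among the named structures was not run, nor was a random effect shared by all facilities in a calendar period. If the df are computed so that they come out near 14, there is no excess. At autocorrelation 0.5 the 5.5% is hardly distinguishable from 5% given the Monte Carlo error.
- **Kenward-Roger already exposes borderline cases.** True, but the reported primary p-value and interval would still be the miscalibrated ones.

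A stronger remedy is tempting: make Kenward-Roger primary. The evidence does not carry it. It was run in only three settings (3.9% and 4.8% without year terms, 4.0% with them). A related model-based test, with Satterthwaite df standing in for Kenward-Roger, gave 4.7–8.1% when only a facility intercept was fitted. When the covariance structure is picked from the data, a jackknife standard error is a defensible primary choice.

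**Conclusion.** The point holds in a limited form. The protocol fixes a jackknife standard error and Satterthwaite df for the same primary test without tying the df to the 15 facilities. If the df come from the model-based variance, type I error under the model as written can reach about 5.5–7%, an excess of at most about 2 points, and the 95% interval is up to 9% too narrow. This rests on an assumed alpha of 0.05, an assumed autocorrelation of 0.5–1.0, and no fixed calendar-period terms.

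A reader might infer that the trial will reject a true null 6–7% of the time. That is too strong: the figure is what the stated rule can produce, not a fixed property of the design, and with calendar-year terms the same rule is slightly conservative. The correction is still worth making, because it concerns the main test and removes the ambiguity in one sentence.

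**What to change.** In Statistical Analysis for Study Objective 1, replace the Satterthwaite sentence, for the primary jackknife test, with facility-based df: refer the jackknife statistic to t with 14 df (number of facilities minus one; critical value 2.14) and build the 95% interval the same way. Keep Kenward-Roger as the planned sensitivity analysis. If calendar-period terms are added to the model, recheck the df by simulation, because 14 df was then conservative.

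**Cost.** No new data and one sentence of text. For a given standard error the interval is at most 2.145/1.96 = 1.094 times as wide, about 9%. For power, on the protocol's own effective sample size the effect divided by its standard error is 0.10/√((0.09 + 0.16)/244.8) = 3.13. Moving the critical value from 1.96 to 2.145 takes nominal power from Φ(1.17) = 88% to Φ(0.98) = 84%. This is a rough guide only, since that formula ignores the mixed model.

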## Study timeline

BSMART is a 5-year study:

Year 1: Protocol approvals will be obtained. A stakeholder meeting will be initiated. Standard operating procedures and manuals will be developed. Training of implementation leaders, lay health worker (LHW) case managers, nurse prescriber-dispensers (NPD), research assistants, and other facility healthcare workers will be conducted. Focus group discussions and Semi-Structured Interviews will be held with study participants, LHW case managers and NPDs.

Year 2: Screening and enrollment will be 12 months. In the trial, each participant will be followed for 24 weeks. Trial quality and compliance will be heavily monitored within the context of intervention implementation, data collection, and data quality.

Year 3: Qualitative studies on trial adoption and implementation delivery will be conducted. Participants' follow-up will be concluded.

Year 4: Analysis of trial primary endpoints and subgroup analysis will be conducted.

Year 5: Preliminary cost evaluation of the intervention will be conducted to focus on integration of the interventions into the HIV care system. Analysis for maintenance at the patient level i.e. durability of the intervention and at the facility level i.e. continuation with the interventions after the withdrawal of the interventions will be conducted. A final stakeholder meeting to focus on dissemination will be held.

|                                                                      | Year 1 |    |    |    | Year 2 |    |    |    | Year 3 |    |    |    | Year 4 |    |    |    | Year 5 |    |    |    |
|----------------------------------------------------------------------|--------|----|----|----|--------|----|----|----|--------|----|----|----|--------|----|----|----|--------|----|----|----|
| Timeline for Major Activities                                        | Q1     | Q2 | Q3 | Q4 |
| Data Management system in place                                      | X      |    |    |    |        |    |    |    |        |    |    |    |        |    |    |    |        |    |    |    |
| Stakeholder Advisory Group & Practitioner Engagement Group Meetings  |        | X  | X  | X  | X      | X  | X  | X  | X      | X  | X  | X  | X      | X  | X  | X  | X      | X  | X  | X  |
| Protocols, surveys, approval                                         |        | X  |    |    |        |    |    |    |        |    |    |    |        |    |    |    |        |    |    |    |

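### The only subgroup method named is separate sex- and age-stratified models, which do not estimate whether the effect differs; a phase-by-factor interaction in the primary model would

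*Protocol*

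**What the plan says.** Under Statistical Analysis for Study Objective 1, after a detailed account of the primary mixed model, the protocol states: "Sex-stratified and age-stratified analyses and models will be performed as secondary analyses". The Study timeline places the work in Year 4: "Analysis of trial primary endpoints and subgroup analysis will be conducted". That second sentence names no method.

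No phase-by-sex or phase-by-age interaction appears anywhere in the protocol. It gives no expected sex split, no age cut or number of age groups, and no rule for interpreting the stratum results. The Hypothesis section lists only overall effects of the intervention and poses no question about effect modification. The analyses are called secondary; they are not called exploratory.

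**The concern.** Fitting the model once in men and once in women answers two questions: what is the effect in men, and what is it in women? It does not answer whether the two effects differ, which is the usual reason for looking at subgroups. With only two separate sets of results, readers tend to notice which stratum is significant and which is not. Each stratum has only part of the sample, so its power is well below that of the whole trial, and a split result can arise by chance when the effect is the same in both.

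The trial is meant to inform deployment through the Ministry of Health and Wellness. A chance impression that the programme works in one sex only could wrongly influence that decision.

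**Working it through.** **Inputs** (Power and Sample size; Study Design)
- Control rate: "the event rate for those in control phase is 10" per cent.
- Effect and power: "our sample of 25 PLWH per cluster per period has power of 87% to detect at least 10% increase", that is 10% against 20%.
- Clustering: "two-sided alpha at intra-cluster correlation of 0.02". The alpha level is not given; 0.05 is assumed.
- Loss: "Assuming withdrawal from trial follow-up or loss to follow-up to be 5" per cent.
- Size: "375 of whom will participate in the pre-implementation phase and 375 of whom will participate in the implementation phase", in 15 facilities.
- Sex split: not given; 50:50 to 80:20 is assumed.

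**Step 1: reproduce the 87%.** After loss, 375 × 0.95 = 356.25 per phase. The design effect is 1 + (25 − 1) × 0.02 = 1.48, so the effective size is 356.25 / 1.48 = 240.7 per phase. For two proportions with the pooled variance under the null, the null standard error is √(2 × 0.15 × 0.85 / 240.7) = 0.03255 and the alternative standard error is √((0.10 × 0.90 + 0.20 × 0.80) / 240.7) = 0.03223. Power = Φ((0.10 − 1.96 × 0.03255) / 0.03223) = Φ(1.12) = 0.869. This agrees with the stated 87%.

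**Step 2: split the information by sex (A).** The noncentrality at 87% power is z(0.87) + 1.960 = 1.126 + 1.960 = 3.086. A stratum with share s of participants has power Φ(3.086 × √s − 1.960). The chance that exactly one sex is significant is p1(1 − p2) + p2(1 − p1). At 50:50, 3.086 × 0.707 − 1.960 = 0.222, so power is 0.588 in each sex and the chance is 2 × 0.588 × 0.412 = 0.485.

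**Step 3: use a design effect for each sex (B).** A stratum has fewer people per facility, so its design effect is smaller: 1 + (23.75s − 1) × 0.02. At 50:50 this is 1.2175, the effective size is 178.125 / 1.2175 = 146.3, and power is 0.670.

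**Step 4: allow for shared facilities (C).** Both sexes attend the same facilities, so the two results are correlated. With v = 0.98 / (23.75s) + 0.02 for each sex, the correlation is 0.02 / √(v1 × v2), which is 0.195 at 50:50 and 0.157 at 80:20. The chance is then p1 + p2 − 2P(both), with P(both) from a bivariate normal. At 50:50 this is 0.670 + 0.670 − 2 × 0.475 = 0.390.

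| Sex split | A: power | A: exactly one | B: power | B: exactly one | C: exactly one |
|---|---|---|---|---|---|
| 50:50 | 0.588 / 0.588 | 0.485 | 0.670 / 0.670 | 0.442 | 0.390 |
| 60:40 | 0.667 / 0.497 | 0.501 | 0.732 / 0.590 | 0.458 | 0.408 |
| 70:30 | 0.733 / 0.394 | 0.550 | 0.782 / 0.489 | 0.506 | 0.464 |
| 80:20 | 0.788 / 0.281 | 0.626 | 0.820 / 0.363 | 0.588 | 0.558 |

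**Sensitivity.** With overall power of 80%, method A gives 0.500 to 0.608 over the same splits. With no design effect at all, the range is 0.370 to 0.596. With the 8-point effect mentioned under Rationale, method B gives 0.500 at 50:50 and 0.533 at 70:30. An interaction test at two-sided 0.05 would wrongly declare a difference in about 5% of trials.

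**Step 5: events in a small stratum.** If one sex makes up 20%, the control phase has 375 × 0.20 = 75 such participants, or 75 / 15 = 5 per facility. At a 10% rate that is about 7.5 control events in total. A separate log-link mixed model would have to estimate its facility and period effects from that.

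**Step 6: power of the interaction.** The variance of the difference between strata is the overall variance divided by s(1 − s). An interaction as large as the overall effect therefore has noncentrality 3.086 × √(s(1 − s)). At 50:50 this is 1.543 and power is Φ(1.543 − 1.960) = 0.34. At 80:20 it is 1.234 and power is Φ(1.234 − 1.960) = 0.23.

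**The case against.** The strongest reply is that the protocol does nothing wrong here. It does not say that strata will be compared, sets no rule for calling one sex responsive, and does not exclude an interaction term. Stratum relative risks with confidence intervals are legitimate description. Interaction tests, age cuts and exploratory labels are commonly left to a statistical analysis plan, and one may exist.

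Much of this stands. A reader might infer that effect differences are to be judged by stratum p-values, or that a misleading split will occur in about half of trials whatever is done. The text supports neither: the first is not stated, and the second depends on a reader dichotomising at 0.05, on the design effect being true and on the sex split. A reader might also infer that each stratum is tested at full alpha, that the covariance structure is chosen again by BIC within each stratum, or that a familywise error rate can be attached to the set of tests. The protocol states no subgroup alpha, describes BIC selection only for the primary-outcome model, and does not say how many age groups there are.

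The reply does not remove the point. The same section fixes the link function, jack-knife standard errors, candidate covariance structures, degrees-of-freedom method and a small-sample sensitivity analysis. At that level of detail, naming stratified models is a choice of method, and that method does not estimate a difference.

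One limit applies to the remedy too. An interaction model adds no events in the smaller sex. It gains by estimating the variance components once, from everyone, and by giving a direct estimate of the difference.

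**Conclusion.** The point holds in a limited form. The one subgroup method that the protocol names cannot show whether the effect differs by sex or age, and a direct alternative is available at little cost. The harm depends on how the results are read. Under a significance-based reading, exactly one sex would be significant in roughly 40% to 60% of trials with an identical effect (39% to 63% across methods A to C). That range assumes alpha 0.05, a true effect of 10% against 20%, and a sex split from 50:50 to 80:20. It applies to sex only; nothing can be computed for age until the strata are defined. The primary analysis is unaffected. The change should be made, but nothing else in the design depends on it.

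**What to change.** Replace the subgroup sentence under Statistical Analysis for Study Objective 1 with wording such as: Effect modification by sex and by age will be examined by adding phase-by-sex and phase-by-age interactions to the primary model fitted to all participants. Each interaction estimate will be reported with its confidence interval, together with the stratum-specific relative risks derived from that model. These analyses are exploratory. Any statement that the effect differs by sex or age will rest on the interaction estimate.

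State how age enters: as a continuous variable or at one cut fixed in advance. If a statistical analysis plan already says this, the protocol need only be aligned with it.

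The cost is a few sentences and one extra model term per factor. The downside is low interaction power (Step 6), so the usual finding will be no clear evidence of a difference. That should be reported as such and not as evidence that the effect is the same.

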## **Randomization methods**

We have chosen 15 (and 4 reserved) high-volume (>1000 HIV-positive patients currently active and on ART) health facilities (See Figure 4) in the ABLE project for inclusion based on numbers of patients, accessibility to the research team, and willingness to collaborate. After a baseline period of 1 year, the BSMART intervention will be implemented in a step of five new randomly selected sites (1 district hospital, 2 primary hospitals, 2 primary care clinics) until it is eventually implemented in all 3 steps (15 sites). A computer-generated list containing facilities stratified by type will determine the order in which the sites receive the intervention. The randomization list will be maintained by a statistician who is not involved in the study, and the site allocation will remain concealed from the research team and clinical teams throughout the study and will be revealed for a given step only 1 month before the implementation of the intervention to allow for training.

[figure not shown]

Figure 4: Selected and reserve facilities for BSMART project

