### Follow-up

Research assistants will fill out follow-up smoking questionnaires at weeks 4, 12 and 24 after the patient receives the SOC brochure. Participants will be provided with breath CO measurements using CO Check+

(coVita) at baseline and then weeks 12 and 24 after enrollment. Participants will also be asked to respond to a semi-structured interview at week 24 that explores challenges to smoking cessation, barriers experienced by participants and reasons for success in those who were able to quit successfully.

| Table 2: Participant Timeline- Control Phase |                    |                                           |        |         |         |
|----------------------------------------------|--------------------|-------------------------------------------|--------|---------|---------|
|                                              | Responsible person | 1 st clinic visit/
Baseline | Week 4 | Week 12 | Week 24 |
| Screening of participants                    | LHW case manager   | X                                         |        |         |         |
| Informed Consent                             | Research Assistant | X                                         |        |         |         |
| Enrollment in BSMART study                   | Research Assistant | X                                         |        |         |         |
| Intake Smoking Questionnaire                 | Research Assistant | X                                         |        |         |         |
| Receipt of SOC brochure                      | LHW case manager   | X                                         |        |         |         |
| Follow-up smoking questionnaire              | Research Assistant |                                           | X      | X       | X       |
| Stages of change                             | Research Assistant | X                                         | X      | X       | X       |
| Breath CO                                    | Research Assistant | X                                         |        | X       | X       |
| Semi-structured Interview                    | Research Assistant |                                           |        |         | X       |

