## Process and Outcome Measures

### 1. Clinical Outcomes

Primary Outcome: The clinical effectiveness endpoint at six months is the 7-day point prevalence abstinence from combustible tobacco products validated primarily by breath CO < 6 ppm. The failure for this measure is any smoking (even a puff) during a 7-day window.

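### The 90-day exclusion for contamination is not tied to enrolment and, on its natural reading, is shorter than the 168 days to the primary endpoint, so some retained controls are assessed after their clinic has switched

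*Protocol*

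**What the plan says.** The contamination check is in the Protocol, Statistical Analysis for Study Objective 1. With contamination given as the reason, it says "we will conduct a sensitivity analysis excluding patients in the control group in the 90 days before crossing over to the implementation group". The text does not say whether a control is placed in the window by enrolment date, by visit date or by being under follow-up.

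The timing it has to match is given elsewhere in the Protocol:

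- Clinical Outcomes: "The clinical effectiveness endpoint at six months is the 7-day point prevalence abstinence from combustible tobacco products".
- Control-phase Follow-up: "Research assistants will fill out follow-up smoking questionnaires at weeks 4, 12 and 24 after the patient receives the SOC brochure". Breath CO is also taken at week 24.
- Study timeline: "In the trial, each participant will be followed for 24 weeks".
- Study Design: "Each step will provide data for a 12-month control/pre-implementation, a 12-month implementation, and a 12-month maintenance period". Table 1 places each step's implementation year directly after its control year, and no transition or washout period is described.
- Randomization methods: a site's allocation "will be revealed for a given step only 1 month before the implementation of the intervention to allow for training".

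**The concern.** A control who enrols late in the control year is still in follow-up when the clinic starts SBIRT and varenicline. The lay health worker case managers who hand out the control brochure deliver SBIRT after the switch, and the workflow text has them meeting existing as well as new patients. Any spillover would most likely raise abstinence among controls and pull the estimated effect toward zero.

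The sensitivity analysis exists to show whether this matters. If it keeps controls whose primary endpoint is read after the switch, a result close to the primary one could be taken as evidence that contamination was unimportant, when part of the opportunity for it is still in the data.

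**Working it through.** **Inputs.** Exclusion window 90 days (Statistical Analysis for Study Objective 1). Endpoint at week 24, so 24 × 7 = 168 days (Follow-up; Study timeline). 375 controls and a 12-month control period (Study Design). Even accrual over 365 days is assumed. The stated 12 months of enrolment supports it, as does the screening rate: 230 per facility per year × 15 facilities × 2 phases = 6,900.

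**1. The mismatch (no accrual assumption).** A control enrolled d days before crossover has the week-24 visit 168 − d days after it.

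- d = 91: 77 days after the switch
- d = 167: 1 day after
- d = 168: on crossover day

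The 90-day window covers the week-12 visit (day 84) but not the visit that defines the endpoint.

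**2. Counts under even accrual.**

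- Week 24 after crossover: 375 × 168/365 ≈ 173 (46%)
- Removed by the 90-day rule: 375 × 90/365 ≈ 92, leaving about 283
- Retained but assessed after crossover: 375 × 78/365 ≈ 80
- Share of those retained: 78/(365 − 90) = 28%

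**3. Post-crossover time.** Under even accrual, control time after the switch is proportional to 168²/2 = 14,112 before exclusion and 78²/2 = 3,042 after it. The share left is 3,042/14,112 = 22%, so the rule removes 78%.

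**4. Other accrual patterns.** If enrolment ran over the nine months (274 days) up to crossover, 375 × 78/274 ≈ 107 would be retained and assessed after the switch. The timeline chart shows three-quarter recruitment blocks with an empty quarter between them. If that quarter (91 days) came just before crossover, the rule would remove almost nobody, and 375 × 77/274 ≈ 105 would still be assessed after it. The chart does not mark crossover dates, so neither pattern can be confirmed.

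**5. Precision.** Power and Sample size states 87% power for 10% against 20%, with 25 per cluster-period, 5% loss and ICC 0.02. The alpha level is not given; 0.05 is assumed.

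- Size per cluster-period after loss: 25 × 0.95 = 23.75
- Design effect: 1 + (23.75 − 1) × 0.02 = 1.455
- Effective n per phase: 15 × 23.75/1.455 = 244.8
- Two-proportion power: 87.5%, which reproduces the stated figure

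Keeping the implementation phase at 244.8 and shrinking only the control clusters:

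| Exclusion | Controls kept (of 375) | Control cluster size after loss | Power |
|---|---|---|---|
| None | 375 | 23.75 | 87.5% |
| 90 days | about 283 | 17.9 | 83.6% |
| 168 days | about 202 | 12.8 | 77.1% |

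This formula makes no allowance for period effects. It is used here only to compare the windows on the protocol's own basis.

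**The case against.** The strongest reply is that the protocol never says enrolled. Read literally, the exclusion could cover anyone under control follow-up at some time in those 90 days. It would then reach back 90 + 168 = 258 days and close the gap, and a SAP could settle the definition. This stands as a limit on certainty. It also shows why the wording needs fixing: under even accrual that reading keeps only 375 × (365 − 258)/365 ≈ 110 controls, against about 283 on the enrolment reading.

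A second reply is that a visit after crossover is not exposure. Research assistants do the control follow-up, varenicline requires referral and clearance by a nurse prescriber, and no text routes an enrolled control into SBIRT. The retained controls have at most 77 days after the switch, about 39 on average. With a quit date on day 8 of treatment and a 7-day abstinence window, a control with less than about two weeks after crossover could hardly reach the endpoint through varenicline. All of this stands, so the 28% is an upper count of opportunity.

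A reader might go further and infer that the 90-day rule leaves contamination essentially untouched, or that 39% of retained controls are exposed once the one-month training lead is counted (108/275). The documents do not support either. The rule removes most of the post-crossover control time. Training is also not delivery: nothing in the protocol makes SBIRT or varenicline available before the crossover date.

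**Conclusion.** The point holds in a limited form. The protocol fixes a 90-day window without saying what it is counted from. On the natural reading, the window is 78 days shorter than the time to the endpoint it is meant to protect. That part needs no assumption about accrual. The figure of about 80 of 283 retained controls (28%) rests on even 12-month accrual and on the enrolment reading, and it counts opportunity rather than exposure. The consequence is incomplete reassurance from one sensitivity analysis. The primary analysis is unaffected, and any residual contamination would most likely work against finding an effect.

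**What to change.** Define the exclusion as controls enrolled fewer than 168 days (24 weeks) before their own facility's crossover date. An alternative is to exclude controls whose actual week-24 assessment falls on or after crossover. This also handles late visits, and otherwise differs only for someone enrolled exactly 168 days before, whose visit is due on crossover day. Controls with no week-24 visit would need the scheduled date. Optionally, repeat the analysis with the one-month training lead added (168 + 30 = 198 days).

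The change needs no new data or visits. Under even accrual it keeps about 202 controls instead of about 283, or about 172 with the training month (375 × 167/365). The interval widens, with power of about 77% against about 84% under the 90-day rule on the protocol's own basis. The retained controls all come from earlier in the control year, so the calendar gap to implementation patients at the same facility grows. That should be stated when the result is reported.
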